## Abstract

**Introduction:**

Multiplathogen home-based self-sampling offers an opportunity to increase access to screening and treatment in endemic settings with high coinfection prevalence of sexually transmitted (HIV, *Trichomonas vaginalis (Tv),* human papillomavirus (HPV)) and non-sexually transmitted pathogens (*Schistosoma haematobium (Sh*)). Chronic coinfections may lead to disability (female genital schistosomiasis) and death (cervical cancer). The Zipime-Weka-Schista (Do self-testing sister!) study aims to evaluate the validity, acceptability, uptake, impact and cost-effectiveness of multipathogen self-sampling for genital infections among women in Zambia.

**Methods and analysis:**

This is a longitudinal cohort study aiming to enrol 2500 non-pregnant, sexually active and non-menstruating women aged 15–50 years from two districts in Zambia with 2-year follow-up. During home visits, community health workers offer HIV and *Tv* self-testing and cervicovaginal self-swabs for (1) HPV by GeneXpert and, (2) *Sh* DNA detection by conventional (PCR)and isothermal (recombinase polymerase assay) molecular methods. *Schistosoma* ova and circulating anodic antigen are detected in urine. At a clinic follow-up, midwives perform the same procedures and obtain hand-held colposcopic images. High-risk HPV positive women are referred for a two-quadrant cervical biopsy according to age and HIV status. A cost-effectiveness analysis is conducted in parallel.

**Ethics and dissemination:**

The University of Zambia Biomedical Research Ethics Committee (UNZABREC) (reference: 1858-2021), the London School of Hygiene and Tropical Medicine (reference: 25258), Ministry of Health and local superintendents approved the study in September 2021.Written informed consent was obtained from all participants prior to enrolment. Identifiable data collected are stored securely and their confidentiality is protected in accordance with the Data Protection Act 1998.

STRENGTHS AND LIMITATIONS OF THIS STUDYThe longitudinal design of the study will allow measurements of incidence and persistence of human papillomavirus (HPV) in association with female genital schistosomiasis (FGS) and HIV and its joint contribution to cervical precancer and cancer.The one-stop home self-sampling (FGS, high-risk HPV) and self-testing (HIV and Trichomonas) approach, if acceptable by participants, can become a scalable integrated screening strategy.Cost-effectiveness data from the study will inform of community-based integration of FGS within the wider sexual and reproductive health screening in Zambia.Recruitment may be limited by stigma pertaining to coexisting sexually transmitted infections.Results may be delayed due to the limited availability of histopathology laboratories.

## Introduction

It is estimated that around 45 million women living in sub-Sahara Africa (SSA) are affected by female genital schistosomiasis (FGS), a chronic, neglected and disabling gynaecological disorder associated with infertility, dyspareunia and symptoms mimicking sexually transmitted infections (STIs).^1 2^ FGS is difficult to diagnose and is part of the wider spectrum of urogenital disease caused by the waterborne parasite *Schistosoma haematobium* (*Sh*). In Zambia, reported FGS prevalence ranges from 33% to 75% of those with urinary schistosomiasis in endemic areas, suggesting a potentially high FGS burden. Data are not yet available on the FGS burden in the general population of Zambia. Furthermore, awareness of the disease and non-sexual mode of transmission is largely absent in endemic communities where information and education are urgently needed.^3^

Conventional FGS diagnosis is challenging as it relies on costly equipment and high-level specialised training which is seldom available in resource-limited countries. Therefore, accurate estimation of disease burden is hindered. However, the past decade has seen a dramatic increase in knowledge generation on many facets of FGS, and particularly on diagnostic strategies closer to the point of care.^4^ Studies have shown acceptable sensitivity of genital swabs for the DNA detection of *Sh* from women’s genital tracts, potentially offering, for the first time, a scalable diagnostic approach for a parasitic disease that has been unacceptably neglected.^3 4^ Genital self-swabs are well accepted by participants and are known to increase uptake across settings.^5 6^

There is a growing evidence of an association of FGS with prevalent HIV, and suggestion of increased incidence and transmission of HIV in the presence of schistosome infections in women.^7^ The lesions and tissue damage caused by FGS can provide an easy route for STI infections.^8^ Further, women with schistosome worm infections and with FGS are potentially far more susceptible and at an increased risk of becoming HIV positive.^9^ However, there is still a knowledge vacuum on the role of STIs in HIV acquisition in the presence of FGS, despite both STIs and *S. haematobium* infection being shown to be independently associated with HIV acquisition.^8 10 11^

There have been small studies suggesting an increased prevalence of high-risk (HR-) human papillomavirus (HPV), the aetiological agent of cervical cancer, in women with FGS compared with those without^12^, higher odds of having an abnormal visual examination with acetic acid (VIA)^13^ and some suggestion of potential links between FGS and cervical cancer.^14 15^ In Zambia, cervical cancer is the most common female cancer, particularly in women aged 15–44 years^16 17^ and with high associated mortality (43.4 per 100 000 women). The lack of accessible screening and treatment programmes^18^ and HPV vaccination contribute to the high cervical cancer incidence in these settings.^19^ HPV-DNA-based tests are recommended for primary screening of cervical cancer as part of the WHO 2021 cervical cancer screening and treatment guidelines,^20^ as better strategies than visual diagnosis.^21 22^ Despite validated self-sampling strategies for the detection of oncogenic or HR-HPV genotypes, community-based screening is not yet widely adopted alone or integrated with screening for other pathogens due to the high cost and infrastructure requirements of currently available tests.^23^

This study protocol describes the development and costing of a community-based comprehensive package for SRH screening in Zambia, including STIs (HPV, HIV, *Trichomonas vaginalis* (*Tv)*) and non-STIs (*Sh*) in different endemicity settings with the long-term aim of preventing life-threatening and disabling conditions such as cervical cancer, HIV and FGS. The overall justification of this study lies in the dearth of research exploring the feasibility of integrated screening and testing strategies for genital coinfections, and the epidemiological associations between them.^24–26^

## Methods and design

### Study design

The Zipime Weka Schista (Do self-testing sister!) study is a longitudinal cohort designed as a holistic approach to FGS detection at scale in the community. The study design will test the hypothesis that integration of home self-sampling for the screening of FGS in conjunction with HR-HPV and self-testing for HIV and STIs is a diagnostically accurate, cost-effective and self-empowering strategy that will increase the detection of cases and improve access to care for women of reproductive age in SSA.

The two main aims of the Zipime Weka Schista study are:

To assess the performance of genital self-sampling, compared with healthcare provider sampling obtained for the detection of *Sh* by molecular testing (real-time PCR and recombinase polymerase assay (RPA)) across two different *Sh* endemicity settings in Zambia.To assess the observed costs of integrating community-based multiple pathogen genital self-sampling (*Sh*, HPV, STIs) and oral self-test (HIV) into a one-stop home intervention and project costs at scale.

Our secondary aims are to explore the epidemiological and immunological interrelationships between FGS and HPV as a potential risk factor for cervical cancer and expand knowledge on HIV acquisition in the presence of coinfections. We will also measure acceptability and feasibility of home-based multiple genital self-sampling and to measure HIV linkage to care and cervical cancer management after home self-sampling and testing. We will further aim to evaluate the effect of FGS and other STI on the diagnostic accuracy of visual inspection for the detection of cervical precancer (CIN2+, CIN3+) and to describe the association of FGS, HPV, HIV and STIs with the presence concentration, diversity and relative abundance of other key cervicovaginal microbiota and infections. We will also aim to consolidate testing for FGS and HPV into one field-applicable multiplex molecular assay and to recruit a subset of male household members of recruited participants screening male genital schistosomiasis.

### Study setting and population

The study is being conducted in Lusaka and Southern provinces of Zambia. The specific study study areas are two sites in Kafue district with high (estimated *Sh* prevalence >70%) and moderate (estimated *Sh* prevalence >50%) prevalence and another site in Livingstone district with low prevalence (estimated *Sh* prevalence <10%). Each woman will have one home visit and one clinic visit at baseline with annual follow-up for 2 years. Enrolment of eligible women began in January 2022 and is expected to be completed in May 2024.

### Inclusion/exclusion criteria

All non-pregnant, sexually active women aged 15–50 years who are currently not menstruating at the time of recruitment and sampling and are able to provide consent are invited to take part in the study. In addition, women should be Zambian residents of the endemic study area for at least 1 year. Women are excluded prior to their sexual debut, pregnant or currently menstruating at the time of recruitment and sampling.

### Sampling strategy and data collection procedures

Community-based cluster sampling was used to obtain a random sample of participants from the study communities. Communities and their households were mapped and each community was subdivided into blocks of approximately 50 households; each one would yield approximately 30 enrolled women. These community blocks were the primary sampling units, with all households in a selected block visited, and all eligible women aged 15–50 years invited to take part. Blocks were randomly selected using random number generation in Stata 18 and are being visited sequentially in the order that they were randomly selected. Participating women are assigned a unique identifier. Field data are entered using the London School of Hygiene and Tropical Medicine (LSHTM) ODK system and uploaded to a secure server in Zambia. The data are then transferred to an LSHTM secure server. The chief investigator is responsible for the data analysis with the support of the Department of Infectious Diseases Epidemiology at LSHTM.

### Sample size and study power

A total of 2500 women will be randomly selected from 2 districts (1250 from each district). Based on previous assessments of FGS using PCR testing of genital samples from women in the study setting, we assume that 5%–10% of genital samples from healthcare provider sampling will have *Sh* detected by molecular testing (5% in the lower endemicity area, 10% in the higher endemicity area). Taking clinic-based sampling as the gold standard, allowing for 10% loss to follow-up between the home and clinic sampling, and assuming that the diagnostic sensitivity and specificity of self-sampling compared with clinic-based sampling for the detection of *Sh* are 70% and 85%, respectively, we will be able to estimate the assumed target diagnostic sensitivity of 70% with a 95% CI of 62.3% to 76.6% overall, and the assumed target diagnostic specificity of 85% with a 95% CI of 83.4% to 86.5% (using the Clopper-Pearson formula to calculate an exact 95% CI for this proportion). Considering individual districts, we will be able to estimate a sensitivity of 70% with a 95% CI of 60.6% to 78.2% in the higher endemicity area and a 95% CI of 55.9% to 81.2% in the lower endemicity area. Corresponding CIs for specificity would be 83%–87% in each area.

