### Statistical analysis

To assess the performance of genital self-sampling compared with healthcare provider sampling for the detection of *Sh,* sensitivity, specificity, positive predictive value (PPV) and negative predictive value (NPV) will be calculated together with 95% CIs. Results will be presented overall and stratified by geographical setting. To explore associations of baseline FGS with the prevalence of cervical precancer at baseline and cervical precancer incidence at 12 and 24 months, logistic regression will be used to estimate ORs. Associations between baseline FGS and HR-HPV persistence at 12 months will be estimated with generalised estimating equation to account for multiple HR-HPV infection and multiple infection states (persistence and clearance).^46^ The association of FGS with HIV acquisition will be assessed using Poisson regression, controlling for key confounders.

Other outcome measures obtained in the study will include (1) HIV incidence rate, HR-HPV clearance and persistence, prevalence and incidence of cervical precancer (histology confirmed CIN2 or CIN3+), measures of association between different exposures (reproductive tract infections); (2) acceptability of multiple genital self-sampling interventions; (3) rates of antiretroviral initiation, continuation of treatment and access to care; (4) cervical precancer diagnosis and treatment, testing and management of STIs; (5) the presence or absence of cervicovaginal microbiota in women with FGS, HPV and STIs. Expressed as relative abundance (percentage abundance of each species), genomic concentration per micro-organism (genome equivalents per mL) and (6) sensitivity, specificity, PPV, NPV of visual inspection of the cervix according to FGS status and integrated molecular field-applicable testing platform for *Sh* and HR-HPV.

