#### Economic analysis

A full economic costing from a provider’s and patient’s perspective is ongoing alongside data collection. Cost data are collected by combining a bottom-up and top-down approach following established costing guidelines,^47^ and STI self-testing economic evaluations in the region. This allows us to estimate the total intervention cost, and unit costs per woman screened, FGS infection detected, per case of CIN2+ detected, per person linked to care, per person successfully treated overall and per pathogen identified. We will model the costs across a set of scale-up scenarios to understand the budget implications of introducing widescale self-screening. Populating a health economics decision model with the study outcomes, we will identify cost thresholds under which joint self-sampling for FGS, HPV, STIs and HIV is cost-effective. This will be relevant for informing the maximum threshold diagnostic kit price based on its potential cost-effectiveness.^48^ MoH and policy-makers will be informed on the most cost-effective screening strategy to implement for FGS screening. This study constitutes the first economic evaluation of FGS.

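### Provider sampling is treated as an error-free reference for self-sampling, so any infection that the self-swab finds and the clinic sample misses is scored as a false positive

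*Protocol article*

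**What the plan says.** The first main aim (Study design) is the performance of self-sampling relative to provider sampling for molecular detection of Sh. Sample size and study power sets the reference by "Taking clinic-based sampling as the gold standard" and assumes that sensitivity and specificity of self-sampling against it "are 70% and 85%, respectively". Statistical analysis adds that "positive predictive value (PPV) and negative predictive value (NPV) will be calculated together with 95% CIs", alongside sensitivity and specificity, overall and by setting.

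Clinic visit names real-time PCR as the reference assay, applied to provider-collected material (two swabs and a lavage). Table 1 lists PCR for Sh DNA on self-swab, provider swab and lavage. The article gives no rule for discordant pairs, no composite reference and no agreement measure for this aim. The blinded re-reading of 10% of samples under Quality control does not alter the reference.

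**The concern.** A gold standard is by definition free of error. Here index and reference are the same kind of test: Sh DNA in a genital sample, collected once at home by the woman and once at the clinic by a midwife. The Introduction says "Studies have shown acceptable sensitivity of genital swabs for the DNA detection of" the parasite but gives no figure, and the Discussion presents self-collected PCR as holding up well against physician sampling. Neither statement supports treating one sample as truth and the other as the test on trial.

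The Study design hypothesis is that the integrated strategy will detect more cases. Under the fixed reference, an additional positive from the self-swab can enter the accuracy table only as a false positive. What is at stake is the meaning of specificity and PPV for the first main aim, and whether the analysis can show a gain in detection if there is one.

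**Working it through.** **Inputs, all from Sample size and study power**

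- "A total of 2500 women will be randomly selected from 2 districts (1250 from each district"
- Clinic-sample positivity: "5% in the lower endemicity area, 10% in the higher endemicity area"; with equal districts, 7.5% pooled.
- "allowing for 10% loss to follow-up between the home and clinic sampling", so 2500 × 0.90 = 2250 pairs, 1125 per district.
- Sensitivity 70%, specificity 85%.

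**Reproducing the plan's intervals.** Reference positives are 0.10 × 1125 + 0.05 × 1125 = 112.5 + 56.25 = 168.75; reference negatives are 2250 − 168.75 = 2081.25. Clopper-Pearson intervals on rounded counts give 62.3% to 76.6% (118/169), 60.6% to 78.2% (79/113) and 55.9% to 81.2% (39/56) for sensitivity. For specificity they give 83.4% to 86.5% overall and about 83% to 87% per district. Every stated interval is matched, so these are the plan's inputs and its interval arithmetic is right.

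**Discordant positives.** The share of self-swab positives that are clinic-negative is (1 − Sp)(1 − p) / [Se·p + (1 − Sp)(1 − p)].

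| | Self+ / clinic+ | Self+ / clinic− | All self+ | Discordant share |
|---|---|---|---|---|
| Overall | 0.70 × 168.75 = 118.1 | 0.15 × 2081.25 = 312.2 | 430.3 | 72.6% |
| Higher area | 0.70 × 112.5 = 78.8 | 0.15 × 1012.5 = 151.9 | 230.6 | 65.9% |
| Lower area | 0.70 × 56.25 = 39.4 | 0.15 × 1068.75 = 160.3 | 199.7 | 80.3% |

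The implied PPV overall is 118.1/430.3 = 27.4%. The planning values put self-swab positivity at 430.3/2250 = 19.1%, against 7.5% at the clinic.

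**How far this depends on the 85%.** Over the corners of the plan's own overall intervals (sensitivity 62.3% to 76.6%, specificity 83.4% to 86.5%) the share runs from 68% to 77%. At an assumed specificity of 95% it is 104.1/(118.1 + 104.1) = 47%; at 99% it is 20.8/(118.1 + 20.8) = 15%.

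**What an imperfect reference would do.** Let g be the share of the 312 discordant positives who are truly infected. This is an assumption; the document gives no value. Take clinic positives as true and suppose that no infection is missed by both samples. Then specificity = 1 − 312.2(1 − g)/(2081.25 − 312.2g), PPV = (118.1 + 312.2g)/430.3, and clinic sensitivity is at most 168.75/(168.75 + 312.2g).

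| g | Specificity | PPV | Clinic sensitivity, at most |
|---|---|---|---|
| 0 | 85.0% | 27% | 100% |
| 10% | 86.3% | 35% | 84% |
| 25% | 88.3% | 46% | 68% |
| 50% | 91.9% | 64% | 52% |

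**What the paired table offers directly.** Clinic-positive, self-negative women number 168.75 − 118.1 = 50.6. The paired difference in detection is (312.2 − 50.6)/2250 = 11.6 percentage points. Its standard error is √[(312.2 + 50.6) − (312.2 − 50.6)²/2250]/2250 = 0.81 points, giving a 95% CI of 10.0 to 13.2 before any allowance for block clustering. This contrast needs no gold standard, although by itself it does not separate extra true infections from extra false positives.

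**The case against.** The stated aim is relative: self-sampling compared with provider sampling. The gold-standard phrase appears only in the sample size paragraph. The 70% and 85% are labelled there as assumed targets used to size intervals. Positive and negative agreement are numerically the same as the planned sensitivity and specificity. Urine microscopy, antigen, lavage and serology are all collected, and an analysis plan that is not shown may use them for discordant pairs.

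Much of this stands. The 73% must be read as a planning figure, and the absence of detailed discordance rules from a condensed article is not a fault. What does not go away is that the article itself fixes the clinic sample as truth and plans PPV against it. PPV is a statement about infection, not about agreement.

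Three stronger readings are tempting but unsupported.

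- A reader might infer that self-sampling is the better method and will be reported as the worse one. No document gives the clinic sample's sensitivity, and some discordant positives may be genuine false positives. If all 312 were infected, clinic sensitivity could be no more than 168.75/(168.75 + 312.2) = 35%.
- A reader might infer that sensitivity must be biased too. It need not be. Assume true prevalence 20%, self-swab sensitivity 70%, clinic sensitivity 50%, perfect clinic specificity and conditional independence. Apparent sensitivity is then (0.20 × 0.70 × 0.50)/(0.20 × 0.50) = 70%, the true value.
- A reader might infer that cost per infection varies 3.6-fold (430/118), according to whether discordant positives count. Economic analysis lists "unit costs per woman screened, FGS infection detected, per case of CIN2+ detected" but does not say that a detected infection needs clinic confirmation, so 118 is not an established denominator.

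**Conclusion.** The point holds in a limited form. The article fixes an error-free reference that its own Discussion gives no reason to accept, and this biases specificity and PPV downward to the extent that the clinic sample misses infections that the self-swab finds. The direction rests on taking clinic positives as true. The size cannot be stated from the document; the table over g shows a range, not an estimate. Positive correlation between two samples from the same woman would make the bias smaller than independence suggests.

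The planning values show why it deserves attention: 312 of 430 self-swab positives (73%) would be discordant, or 47% at an assumed 95% specificity. The sample size and its intervals are not in question. This is an inexpensive improvement to the analysis and its wording, not a defect in the design.

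**What to change.** 1. Keep the planned comparison, but describe it as positive and negative percent agreement with provider sampling, and remove the gold-standard label.
2. Add the paired difference in detection (self-swab minus provider sample) with a 95% CI that allows for clustering by block, since blocks are the primary sampling units.
3. Sensitivity analysis (a): take as reference Sh DNA by PCR in any clinic specimen, provider swab or lavage. If clinic-based sampling already means this, say so. It reduces the bias only in part, because a woman positive on the self-swab and negative on every clinic specimen still counts as a false positive.
4. Sensitivity analysis (b): a latent class model of self-swab, provider swab and lavage with a stated dependence assumption. Three binary tests give 2³ − 1 = 7 free cells, and independence already uses 7 parameters (one prevalence, three sensitivities, three specificities). Dependence between swab and lavage from the same visit therefore needs a further restriction. One option is accuracy common to both districts, which gives 14 cells for 8 parameters.

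No new samples or assays are needed, since Table 1 already lists PCR on all three specimens. The cost is wording and code, a second set of figures for readers to reconcile, and a model assumption that the data can test only in part.

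### The planning confidence intervals carry no design effect for the block sampling, so they are too narrow under any positive within-block correlation, mainly for specificity

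*Protocol article*

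**What the plan says.** The protocol article's section on sampling strategy and data collection procedures describes a one-stage cluster sample: "Community-based cluster sampling was used to obtain a random sample of participants from the study communities". Communities are divided into blocks of about 50 households. On these it says "These community blocks were the primary sampling units, with all households in a selected block visited", with all eligible women invited, and "each one would yield approximately 30 enrolled women".

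The section on sample size and study power describes the selection in terms of individual women: "A total of 2500 women will be randomly selected from 2 districts (1250 from each district"). It assumes detection of *S. haematobium* in provider samples of "5% in the lower endemicity area, 10% in the higher endemicity area", sensitivity of 70% and specificity of 85%, "allowing for 10% loss to follow-up between the home and clinic sampling". The method is stated as "using the Clopper-Pearson formula to calculate an exact 95% CI for this proportion". The resulting 95% intervals are:

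- sensitivity: 62.3–76.6% overall, 60.6–78.2% in the higher area and 55.9–81.2% in the lower area;
- specificity: 83.4–86.5% overall and 83–87% in each area.

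The section mentions no ICC, design effect or cluster size.

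The statistical analysis section promises 95% CIs for the accuracy measures. For cervical precancer "logistic regression will be used to estimate ORs", and Poisson regression is planned for HIV acquisition. Generalised estimating equations (GEE) are planned for HPV persistence, to handle multiple infections and infection states. Blocks are not mentioned there.

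**The concern.** The Clopper-Pearson interval is exact for independent observations. When women enter the sample as whole blocks, results within a block may be correlated, and the information in the sample is then less than the count of women suggests. The accuracy of genital self-sampling is one of the study's two main aims, so these intervals are its headline statement of precision. If they leave out the design effect, the plan promises more precision than its own sampling scheme supports. If the analysis intervals were computed in the same way, their coverage would fall below 95%.

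The correlation that matters here is that of self/provider agreement within a block, among women with the same reference result. This differs from clustering of infection itself. Home visits are run by community workers who demonstrate the self-swab, and women of one household can all be enrolled. Shared influences on swab quality are therefore possible, but the article does not quantify them.

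**Working it through.** **Inputs from the article.** 1250 women per district; 10% lost between home and clinic; reference prevalence 10% and 5%; sensitivity 70%; specificity 85%; about 30 enrolled women per block.

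**Denominators.**
- Analysed women per district: 1250 × 0.9 = 1125.
- Reference-positive: 1125 × 0.10 = 112.5 and 1125 × 0.05 = 56.25, together 168.75.
- Reference-negative: 1012.5 and 1068.75, together 2081.25.

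**Reproducing the stated intervals (Clopper-Pearson, no design effect).**

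| Quantity | Count used | Recomputed | Stated |
|---|---|---|---|
| Sensitivity, overall | 118/169 | 62.3–76.6% | 62.3–76.6% |
| Sensitivity, higher area | 79/113 | 60.6–78.2% | 60.6–78.2% |
| Sensitivity, lower area | 39/56 | 55.9–81.2% | 55.9–81.2% |
| Specificity, overall | 1769/2081 | 83.4–86.5% | 83.4–86.5% |
| Specificity, higher area | 861/1013 | 82.7–87.1% | 83–87% |
| Specificity, lower area | 908/1069 | 82.7–87.0% | 83–87% |

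All agree, so no allowance for clustering is hidden in the figures.

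**Adding the design effect.** Blocks: 2500/30 ≈ 83, or about 42 per district. With m the mean number of women per block in the relevant denominator:

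DEFF = 1 + (m − 1) × ICC, and n_eff = n/DEFF.

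The interval is recomputed at n_eff. The ICC range of 0.01 to 0.10 is an assumption.

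*Specificity, overall:* m = 2081.25/83.3 ≈ 25.

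| ICC | DEFF | n_eff | 95% CI | Width (points) |
|---|---|---|---|---|
| 0 | 1.00 | 2081 | 83.4–86.5% | 3.1 |
| 0.01 | 1.24 | 1679 | 83.2–86.7% | 3.5 |
| 0.02 | 1.48 | 1407 | 83.0–86.8% | 3.8 |
| 0.05 | 2.20 | 947 | 82.6–87.2% | 4.7 |
| 0.10 | 3.40 | 613 | 81.9–87.7% | 5.8 |

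The standard error grows by a factor of √1.24 = 1.11 to √3.40 = 1.84.

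*Specificity, by district:* m ≈ 24.3 (higher) and 25.7 (lower). At ICC 0.01 the interval is about 82.4–87.4%, at 0.05 about 81.4–88.1%, and at 0.10 about 80.5–88.8%.

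*Sensitivity, overall:* m = 168.75/83.3 ≈ 2.0. At ICC 0.10, DEFF = 1 + 1.025 × 0.10 ≈ 1.10 and the interval is 62.1–77.1%. The like-for-like comparator, centred on exactly 70%, is 62.5–76.8%; the stated interval is centred on 118/169 = 69.8%. The width goes from 14.3 to 15.1 points.

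If positives are also concentrated in some blocks (assumed squared coefficient of variation of 1 in the number of positives per block), DEFF = 1 + (2 × 2.025 − 1) × 0.10 ≈ 1.30 and the interval is 61.3–77.7%.

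*Sensitivity, by district, ICC 0.10, positives evenly spread:* DEFF is 1.17 in the higher area (59.8–78.9%) and 1.03 in the lower area (56.1–81.7%).

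**The case against.** The strongest reply has four parts.

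- **There is no arithmetic error, and the stated precision may be nearly right.** The binomial arithmetic is indeed correct. The loss depends on an ICC that the article does not give. At 0.01 the overall specificity interval moves by about 0.2 points at each end, and even at 0.10 it stays within about 3 points of 85%. This stands, and it limits the size of the point. It does not remove it, because the intervals rest on zero within-block correlation, which the article neither states nor defends.
- **Focal infection is not clustering of errors.** Each self-swab is compared with a provider swab from the same woman, so a shared water source does not by itself correlate the misclassification. This also stands. It is why the ICC is treated as an assumption and shown as a range.
- **The scarcer quantity, sensitivity, hardly changes.** Correct.
- **No threshold depends on these intervals.** The section gives expected precision, with no test or success margin that could be reversed. Correct, and it keeps the consequence to one of stated precision.

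A reader might go further and infer that the standard errors of the association analyses will be too small. The article does not support that. It names the models but no variance estimator, and an analysis plan that is not shown may specify block-robust errors. Nor does it show that female genital schistosomiasis varies mainly between blocks, since no between-block variance is given.

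**Conclusion.** The point holds for the planning intervals. The sampling section describes a cluster sample and the sample size section gives the precision of an independent one. An analysis plan cannot repair this, because the figures in the sample size section are already fixed without a design effect. They are too narrow for any positive within-block correlation of self/provider agreement.

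The consequence falls mainly on specificity. Over an assumed ICC of 0.01 to 0.10 its overall interval widens from 3.1 points to between 3.5 and 5.8 points, and the district intervals widen from about 4.5 to between about 5 and 8.3 points. Sensitivity widens by less than 1 point overall, or by about 2 points (14.3 to 16.4) if positives are also concentrated in some blocks. These figures assume about 30 women per block and 10% loss spread evenly over blocks.

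For the regression models the article supports a narrower statement: blocks are not mentioned, and the one correlation it does address, through the GEE, is between infections and infection states. That calls for a clarification; it is not a demonstrated error.

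**What to change.** 1. In the sample size section, state an ICC or a design-effect range with its basis, and restate the sensitivity and specificity intervals accordingly, overall and by district. Describe the selection as a cluster sample of blocks there too.
2. In the statistical analysis section, state that the accuracy measures and their intervals are computed with block as primary sampling unit and site as stratum, for example with a Korn-Graubard interval, which adapts Clopper-Pearson to clustered samples.
3. State that the logistic, GEE and Poisson models use block-clustered robust standard errors. If the analysis plan already says so, a cross-reference is enough.

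The block is already the sampling unit, so no new data or recruitment is needed. The cost is some wording, a change of variance method and slightly wider stated intervals.
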